**Adolescents and young adults living with HIV**			
Eligibility assessment		X	X
Informed consent/assent		X	X
Exit interviews		X	
Survey questionnaire			X
Specimen collection^a^			X
**Adolescent caregivers**			
Eligibility assessment		X	
Informed consent		X	
Semi-structured interviews		X	
**Healthcare workers and key informants**			
Eligibility assessment^b^	X		
Informed consent ^b^	X		
Semi-structured interviews	X	X	X
Costing questionnaires	X	X	
**Site-level activities**			
Direct clinic observation		X	
Collection of process indicators (monitoring of intervention fidelity/uptake)		X	
Abstraction of routine data			X

^a^Real-time viral load testing and stored samples

^b^In the event that a HCW or KI leaves a study site, the new staff member at the site will be enrolled as a replacement

#### AYAHIV

Up to 2400 AYAHIV (maximum of 200 AYAHIV per site) will be recruited to take part in a one-time post-intervention assessment at 12 months post-intervention implementation and up to 720 AYAHIV (maximum of 60 per site) in exit interviews during intervention implementation. Clinic staff will work with on-site study staff to review the daily schedule and list potentially eligible AYAHIV who have appointments. During the clinic visits at the 12 sites, clinic staff will consecutively approach and directly present the study to those 18 years and older or the adult caregiver for adolescents younger than 18. Both interested AYAHIV and caregivers will be referred to the study staff for recruitment. The study staff will give AYAHIV more details on the study procedures, screen AYAHIV for eligibility using criteria in Table 1, and finally obtain informed consent from AYAHIV 18 years and older or assent from adolescents aged 12–17 of consenting caregivers. Eligible adolescents aged 10–11 will be given information sheets that describe the study, and consent for their participation will be obtained from their caregivers. The study staff will note reasons for ineligibility and/or refusal and AYAHIV will be replaced until target sample is reached at each site.

#### Caregivers

Up to 120 AYAHIV caregivers (up to 20 per intervention site) will be recruited to participate in semi-structured interviews after attending caregiver-specific support groups during the intervention implementation. The facilitators leading the support groups will identify caregivers to participate in post-support group interviews, present the potential participation in the interviews directly to caregivers, and refer interested caregivers to on-site study staff to learn more about the interview procedures. If interested in participating, caregivers will be screened based on the criteria in Table 1, and those found eligible and agree to participate will undertake the informed consent process.

#### HCW and KI

Up to 112 HCWs and 60 KIs will be recruited to participate in semi-structured interviews before, during, and after intervention implementation. In addition, a subset of up to 50 HCWs enrolled in semi-structured interviews will be asked to complete an additional costing questionnaire at multiple time points before and during intervention implementation. The study team will meet with the administration at each study site to gain permission to invite HCWs to participate in interviews. Once approval is granted, the study will be introduced to the HCWs at routine staff meetings. Staff interested in the study will receive additional information about the interview from the study team and, if interested in participating, HCWs will be screened based on the criteria in Table 1. Those who are deemed eligible and agree to participate will undertake the informed consent process. HCWs will be assured that their decision to participate will not impact their employment status.

The study team will compile a list of KIs who can be invited to participate in pre/post-intervention interviews. KIs will include ICAP project staff, health facility directors, and staff from regional health offices and MISAU, who will provide their perceptions about implementing the study intervention at a managerial level. Once contacted, all KIs who express interest in learning more will be given basic interview participation information. If interested, they will be screened based on the criteria in Table 1. Those who are eligible will undertake the informed consent process.

For all other participants (HCWs, KIs, caregivers), purposeful sampling will be used, recruiting participants that have been directly involved in the implementation and who are interested in sharing their views with our study interviewers.

### Interventions

The intervention design is based on extensive formative research with AYAHIV, HCWs, AYAHIV caregivers, and other key stakeholders in this setting. Preliminary work included implementation science (quantitative surveys, qualitative interviews) and human-centered design methods, under which AYAHIV and stakeholders including AYAHIV participated in an intensive, iterative process of testing and refinement to develop a multi-component intervention strategy, the CombinADO strategy [14]. Once developed, this strategy was piloted with AYAHIV, caregivers, and HCWs to demonstrate the various intervention components’ acceptability and feasibility. Based on this formative phase’s findings, we designed a multi-component package of intervention modalities that will be delivered as part of enhanced services for AYAHIV at intervention sites. Both the control and intervention conditions will be in place at the study sites for 12 months. A complete list of control and intervention components and each component’s rationale is outlined in Table 3.

**Table 3 Tab3:** CombinADO study arm components during the 12 months of implementation

Component	Rationale	Study arm	
		Control	Intervention
Radio ads	Engaging radio mini shows that address community stigma and medical literacy through busting common myths with humor and building empathy with heartfelt storytelling	X	X
Community sensitization campaign	Large-scale, infographic billboards and posters located in public areas and secondary schools to address stigma and medical literacy and promote community support for AYAHIV	X	X
Informational posters	Large-scale, infographic posters located in clinic waiting areas to normalize HIV and build confidence in treatment	X	X
Motivation walls	Interactive, patient-generated posters located in the consultation room where patients can post words and phrases about themselves and their futures	X	X
Pill boxes	A discreet pill container to support ART adherence	X	X
CombinADO-specific AYAHIV training	Comprehensive in-service training for healthcare workers	X	X
One-stop shop	Combined adolescent and HIV services	X	X
Treatment toolkit	A guide to clinic visits and discussions on Art and viral load monitoring to help HCW better communicate with patients	X	X
Self-reflection kit	A simple handout for providers to help patients reflect on their ART progress and understand the concept of viral load as a measure of ART success	X	X
Peer support at clinical level	Peer exposure to examples of AYAHIV openly living with HIV and opportunities to share their experiences with HIV in one-on-one interactions with other AYAHIV during clinic visits		X
Informational and motivational video	An informational and motivational video that in simple language with engaging graphics that (a) demystifies and simplifies HIV, ART, and viral load and (b) emphasizes that people can live long, healthy lives		X
Support groups for caregivers of AYAHIV	A learning, support, and empowerment group for caregivers of AYAHIV. Through monthly gatherings, the program aims to foster confidence and equip caregivers with strategies to support AYHIV adherence journey		X
Support groups for AYAHIV	A peer-to-peer learning, support, and empowerment group to address loss of hope and improve medical literacy. Through biweekly gatherings, the program aims to foster belonging and confidence, equipping young people and caregivers with strategies to navigate the adherence journey		X
Mental health screening and linkage to adolescent-focused mental health support	HCWs will be trained in the use of a brief mental health screening tool focusing on depression, anxiety, and post-traumatic stress disorder. Mental health service providers at each facility will be trained and supported to provide diagnostic and mental health support to youth with positive screens who agree to further evaluation		X

#### Description of the control condition (optimized SOC)

The control condition will be implemented at all 12 clinic sites and includes a set of interventions aimed at optimizing the national standard of care, including (1) billboards/posters and radio shows, (2) healthcare worker training, (3) one-stop adolescent and youth-friendly services, (4) information/motivation walls, (5) pill containers, and (6) tools to be used by clinic staff during clinical visits (Fig. 1 and Table 3).

**Fig. 1 Fig1:**
[figure not shown]
CombinADO study design for the clinic-level clusters: purple areas indicate the control conditions (optimized standard of care) and the blue indicates intervention conditions (enhanced intervention)

#### Description of the intervention condition (enhanced intervention)

The intervention condition will be superadded to the control condition at six randomly selected clinic sites and includes the following five additional intervention components: (1) peer support, (2) informational and motivational video, (3) support groups for caregivers of AYAHIV, (4) support groups for AYAHIV, and (5) mental health screening and linkage to adolescent-focused mental health support (Fig. 1 and Table 3).

### Randomization and blinding

Randomization will be balanced 1:1, with an equal number of study sites randomized to each arm.

A randomization list will be prepared by the independent statistician and passed to the study team. The intervention allocation is open to the study team and will not be blinded to investigators or HCWs and AYAHIV participating in the trial. However, all staff involved in data analysis will be blinded to arm allocation, including the trial statistician. To facilitate this, we will maintain separate databases for variables collected only at intervention sites (including process evaluation measures), independent from data on primary and secondary outcomes collected at intervention and control sites in an identical manner. In addition, laboratory staff involved in measuring the primary outcome will also be blinded to arm allocation.

The independent statistician will maintain randomization codes, and unblinding of the analysis team will occur only after final results using dummy randomization allocation have been completed by the study statistician. As the study team is unblinded to allocation, they will be able to address any issues related to adverse events. If the trial statistician or other personnel working in data analysis become unblinded prematurely for any reason, the principal investigator (PI) and investigator team will be notified immediately. Potential biases introduced through inadvertent unblinding will be examined, along with strategies to mitigate the impact of this on trial reporting.

### Study outcomes

The trial outcomes are described in Table 4 and include effectiveness outcomes and implementation outcomes summarized below.

**Table 4 Tab4:** Study objectives and justification for the study endpoints

Objectives	Endpoints	Justification for endpoints	Putative mechanisms of action
**Primary**			
To evaluate the efficacy of the CombinADO strategy on the rate of HIV viral suppression among AYAHIV receiving HIV care at 12 health facilities in Nampula Mozambique	Viral suppression < 50 copies/mL at 12 months among AYAHIV in care at intervention and control sites	HIV viral suppression is a major goal of effective ART services, is readily measured, and is a well-established as the gold standard outcome to evaluate HIV treatment interventions	The CombinADO strategy is hypothesized to increase viral suppression through increases in retention in care and/or adherence to ART in the target population
**Secondary**			
To evaluate the efficacy of the CombinADO strategy on the rate of retention in care among AYAHIV receiving HIV care at 12 health facilities in Nampula Mozambique	Retention in care defined as objective evidence of engagement in the preceding 90 days among AYAHIV in care at intervention and control sites	Increases in retention in care is a causal intermediate (mediator) through which the CombinADO strategy may increase HIV viral suppression	Different elements of the CombinADO strategy are likely to support AYAHIV’s retention in care during the intervention period
To evaluate the efficacy of the CombinADO strategy on the rate of adherence to ART among AYAHIV receiving HIV care at 12 health facilities in Nampula Mozambique	Self-reported using the Wilson measure; TDF levels on a subset of participants in care, selected retrospectively in a case-control substudy comparing AYAHIV who have VL < 50 copies/mL, versus those with VL ≥ 50 copies/mL	Increases in ART adherence is a causal intermediate (mediator) through which the CombinADO strategy may increase HIV viral suppression	Different elements of the CombinADO strategy are likely to support AYAHIV’s adherence to ART during the intervention period
To assess the uptake, feasibility, and acceptability of the CombinADO strategy at 12 health facilities in Nampula Mozambique	Uptake and utilization of intervention components by AYAHIV among AYAHIV in care at intervention and control sites; implementation fidelity by health care workers and key informants	Uptake and implementation of the intervention is an intermediate (mediator) through which the CombinADO strategy may increase HIV viral suppression	Inadequate uptake and implementation of the intervention and/or components can limit efficacy of the intervention
To estimate the cost and incremental cost-effectiveness of the CombinADO strategy at 12 health facilities in Nampula Mozambique	Incremental cost per additional case of viral suppression < 50 copies/mL at 12 months	HIV viral suppression provides an objective summary measure of intervention effectiveness	The CombinADO strategy is hypothesized to increase viral suppression through increases in retention in care and/or adherence to ART in the target population

#### Effectiveness outcomes

The primary outcome is viral suppression < 50 copies/mL at 12 months post-intervention implementation among AYAHIV at intervention and control sites, which will be assessed through real-time viral load testing.

Secondary outcomes include:

(1) ART adherence will be measured by using a validated Wilson self-report ART adherence measure administered on all AYAHIV participating in the one-time post-implementation assessment at 12 months post-intervention implementation [26, 27]. In addition, TDF levels will be measured on a subset of participants in care selected retrospectively in a case-control sub-study comparing AYAHIV who have VL < 50 copies/mL, versus those with VL ≥ 50 copies/mL. The Wilson measure has previously been implemented in this setting to assess ART adherence among AYAHIV during the first phase of the CombinADO study [12]. (2) Retention in care will be measured as objective evidence of engagement in the preceding 90 days among AYAHIV in care at intervention and control sites abstracted from routine clinic records.

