#### Statistical analysis

Descriptive statistics will be presented with frequency (percent) or median (interquartile range) depending on the type and will provide overall and by allocation arm. Review of data distributions will be undertaken prior to applying any inferential statistics requiring specific assumptions and methods revised or corrective procedures undertaken. Covariates and specific details of analysis will be fully specified before database closure in a detailed SAP developed by the study statistician and study team. All statistical tests will be two-sided with nominal *α* = 0.05. Study endpoints are binary and will be approached in a similar way. The primary outcome analysis will compare AYAHIV virologic suppression at 12 months post-intervention implementation in intervention versus control sites using generalized estimating equations under a binomial model, with a log link and robust standard errors, providing unbiased marginal estimates of the intervention effect while adjusting for within-cluster correlations. Clustering will be by site using an exchangeable correlation structure. Estimates will be reported as risk ratios (RR) with robust 95% confidence intervals and *p*-values assessed at *α* = 0.05 for all comparisons. No additional adjustment variables will be included in the primary analysis. In subsidiary analyses, we will include covariate adjustment based on confounders selected a priori using direct acyclic graphs. Sensitivity analysis will address potential heterogeneity in clustering by evaluating endpoint models under different assumed correlation structures. Missing outcome data will be handled by complete case analysis in the first case and then by sensitivity analysis substituting alternate outcome values for missing data. Missing data in covariates will be handled by multiple imputations using chained equations. Analysis of secondary endpoints is not conditional on the outcome of the primary endpoint. Secondary endpoints will be approached identically as the primary endpoint. Planned subgroup analyses, which include by age group [10–14, 15–19, 20–24], sex, pregnancy status during the intervention period among females, duration of prior ART use, and ART regimen, will be carried out for primary and secondary outcomes using the same approach as the previously described. Exploratory analyses will include:

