#### Secondary outcomes

##### Adherence

Projected statistical power for comparing the secondary adherence outcomes between intervention versus control sites uses the same assumptions as above, thus having similar expectations around achieved power and minimal detectable differences.

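### TDF level is an adherence efficacy endpoint, but it is measured in a subset selected on viral load and no weighting is stated, so an arm comparison as written would in general be biased

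*Protocol article*

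**What the plan says.** In the protocol article, the secondary part of Table 4 states the objective "To evaluate the efficacy of the CombinADO strategy on the rate of adherence to ART among AYAHIV receiving HIV care". One of the two endpoints listed for it is "TDF levels on a subset of participants in care, selected retrospectively in a case-control substudy comparing AYAHIV who have VL < 50 copies/mL", against those at or above that threshold. The Effectiveness outcomes section repeats the selection: "TDF levels will be measured on a subset of participants in care selected retrospectively in a case-control sub-study". The Abstract also counts TDF levels among the secondary outcomes.

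The Statistical analysis section says "Study endpoints are binary and will be approached in a similar way" and "Secondary endpoints will be approached identically as the primary endpoint". For the primary endpoint the method is a log-link binomial GEE clustered by site, and "No additional adjustment variables will be included in the primary analysis". Sampling weights are not mentioned, and TDF is not excepted.

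Populations for analyses assigns the adherence outcome to everyone who agrees to the 12-month assessment and has both a questionnaire and a viral-load result. The Adherence paragraph under Sample size and power refers to adherence outcomes in the plural, compared between intervention and control sites, and says the projected power "uses the same assumptions as above, thus having similar expectations around achieved power and minimal detectable differences". No sampling ratio and no size are given for the TDF subset.

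**The concern.** An efficacy objective calls for a comparison between arms. Table 4 describes adherence as a mediator through which the strategy may raise suppression, so viral load lies downstream of what TDF measures. It is also expected to differ by arm. Choosing whom to test on viral load therefore changes the mix of suppressed and unsuppressed participants in each arm's sample. An unweighted proportion in that sample is then not the proportion adherent in that arm.

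At stake is the one biological adherence measure named as an endpoint, in a trial where participants know their allocation and self-report could be influenced by it. A distorted TDF contrast could wrongly contradict or wrongly support the self-report result.

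**Working it through.** **1. The plan's own figure.** No figure is given for TDF. The only number carried over to adherence is the power above 80% for the primary outcome (12 clinics, 100 each, 65% v 81%, ICC 0.05).
- Design effect: 1 + 99 × 0.05 = 5.95.
- Effective number per arm: 600 / 5.95 = 100.8.
- Two-sided pooled test at 0.05: power 0.73. With ICC 0.04 (design effect 4.96, 121.0 effective per arm) it is 0.80.

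The shortfall at ICC 0.05 is a separate matter, and nothing below depends on it. What matters here is that the statement rests on about 100 participants per clinic.

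**2. Inputs for the TDF check.** Suppression of 65% in control and 81% in intervention comes from Sample size and power (65% plus 16 points). Arms are taken as equal in size, in line with the 1:1 clinic allocation. TDF is treated as adherent or not, because the endpoints are said to be binary. The document does not link TDF to viral load numerically, so those probabilities are assumptions.

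**3. Formula.** Let s be the suppressed share of an arm's sample, a = P(adherent | suppressed) and b = P(adherent | unsuppressed). The expected adherent proportion is s·a + (1 − s)·b.

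**4. Case with a = 0.90 and b = 0.40 in both arms.**
- Whole arm (s = 0.65, 0.81): 0.65 × 0.90 + 0.35 × 0.40 = 0.725; 0.81 × 0.90 + 0.19 × 0.40 = 0.805. RR = 1.11.
- 1:1 within arm (s = 0.50 in both): (0.90 + 0.40)/2 = 0.65 in both. RR = 1.00.
- 1:1 pooled over arms: all unsuppressed, plus a fraction (0.35 + 0.19)/(0.65 + 0.81) = 0.54/1.46 = 0.370 of the suppressed. This gives s = 0.407 and 0.612, so 0.604 v 0.706. RR = 1.17.

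Other values of a/b: with 85/50, true RR 1.08, within-arm 1.00, pooled 1.11. With 95/30, true 1.14, within-arm 1.00, pooled 1.24. The within-arm value is 1.00 every time because a and b are held equal across arms, so these rows are not a sensitivity range for that result.

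**5. Modelling in the protocol's causal direction.** Fix u = P(suppressed | adherent) and v = P(suppressed | not adherent) across arms. Adherence in an arm with suppression p is A = (p − v)/(u − v). Then a = A·u/p and b = A·(1 − u)/(1 − p), which now differ by arm.

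For u = 0.90, v = 0.30:
- Control: A = 0.35/0.60 = 0.583, a = 0.808, b = 0.167.
- Intervention: A = 0.51/0.60 = 0.850, a = 0.944, b = 0.447.
- True RR 1.457. Within-arm 1:1 gives 0.487 v 0.696, RR 1.428.

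| u / v | True RR | 1:1 within arm | 1:1 pooled |
|---|---|---|---|
| 0.98 / 0.05 | 1.267 | 1.065 | 1.528 |
| 0.90 / 0.30 | 1.457 | 1.428 | 1.757 |
| 0.85 / 0.35 | 1.533 | 1.624 | 1.849 |

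Within-arm sampling can pull strongly to the null, do little, or push slightly away from it. Pooled sampling moved the estimate away from the null in every case tried.

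**6. Effect of weighting.** Weighting each tested participant by the inverse of the sampling fraction for their viral-load group restores s to 0.65 and 0.81. In step 4 that returns 0.725 v 0.805, RR 1.11.

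**The case against.** The strongest reply is that the article never says outright that TDF will be compared by arm without weights. The one contrast attached to the sub-study is suppressed against unsuppressed, and for that contrast selecting on viral load is a sound design. The sentence about analysing secondary endpoints like the primary is general. TDF levels have no stated cut-off, and the adherence population fits the self-report measure better. The article also defers analysis details to an SAP that is not shown, and weights could be set there.

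Much of this stands. If the viral-load contrast is the only TDF analysis, no biased arm estimate arises. But TDF then does not answer the objective it is listed under, and the general analysis sentence and the plural adherence power statement need an exception. The passages must be reconciled on either reading.

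Three stronger inferences are tempting, and the document does not support them:
- *The sampling removes a real effect by design.* The exact null needs equal numbers within arm and identical TDF-given-viral-load probabilities in both arms. Neither is stated, and the second fits poorly with adherence driving suppression (step 5).
- *A subset cannot have the stated power.* The carried-over assumption is about 100 per site, while up to 200 per site may be recruited. With ICC 0.05, even 50 per site gives 300/(1 + 49 × 0.05) = 87 effective per arm, against 101. The claim is unsupported for TDF because no subset size is given; it is not shown to be impossible.
- *TDF is the only objective adherence information.* Pharmacy dispensing and refill data are also abstracted, although they are not a named endpoint.

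**Conclusion.** The point holds as a limited one. The article places TDF under an efficacy objective, selects the TDF subset on the primary outcome, and prescribes the primary analysis for secondary endpoints with no exception. Carried out literally, that arm contrast does not estimate adherence in either arm unless both viral-load groups are sampled at one fraction, in which case the sample is no longer case-control.

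The size cannot be fixed from the document. In the 90%/40% illustration a true RR of 1.11 reads as 1.00 or 1.17 depending on the sampling. In the causal-direction cases the within-arm distortion runs from 1.267 read as 1.065 to 1.533 read as 1.624. All of these rest on assumed links between TDF and viral load and on assumed 1:1 schemes. The consequence is confined to one component of one secondary outcome.

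**What to change.** Choose one of the following and state it in the protocol or SAP before any samples are selected for testing:
- Draw the TDF subset at random within site, regardless of viral load, and compare arms as for the other secondary endpoints.
- Keep selection on viral load, record the sampling fractions by viral-load status and site, and use an inverse-probability-weighted GEE for any arm contrast. The unweighted case-control comparison then serves only the association between TDF and viral load.
- Remove TDF from the efficacy endpoints in Table 4, the Abstract and Effectiveness outcomes, label it as a study of the TDF-viral load association, and except it from the general sentence on secondary endpoints.

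In each case, restrict the adherence power statement to the self-report measure and give the planned size of the TDF subset.

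The cost is wording and record-keeping. Dried blood spots are taken at the 12-month assessment and stored until testing at the end of the study, so no new samples are needed. Weighting gives somewhat wider intervals. Random selection yields fewer unsuppressed participants for the association analysis. If the fractions are not recorded at selection, weighting may not be recoverable later.
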